### The intervention

The intervention is based on *the Representational Approach to patient education* developed by Donovan and co-workers. This approach combines two theories. The *common sense model of illness representations* provides a framework for a thorough assessment of the parents’ knowledge of the topic in question. The mental representation of an illness consists of the following six dimensions: identity, cause, timeline, consequences, cure/control, and emotion. Before giving information, the parents’ representations are assessed by the nurse to find gaps, misunderstandings, or confusion in those representations. This then guides the nurse in tailoring the education session for each individual. To alter a representation, another theory about *conceptual change* is used, and this implies that it is crucial to understand the consequences from the knowledge gaps or confusion before providing information to the patient. This method has been used previously in adult services such as oncology and cardiac surgery [28, 29] and was also shown to be useful in the pilot testing of this intervention [18].

Two registered children’s nurses at each site have been employed part-time to deliver the intervention. All have specialist training in paediatric nursing and several years of experience in paediatric oncology. Before the intervention started, they took part in a three-day training workshop that included both theoretical sessions and practical training in the intervention method. They were also provided with a booklet outlining the principle content of the method (available from the authors).

Each parent in the intervention arm has four meetings with the intervention nurse, and before each meeting the parent chooses a topic of interest. A list of suggested topics is available for this, based on topics chosen by parents in the pilot study and during a workshop with clinically experienced nurses in paediatric oncology. The parent can also pick a topic on their own or get suggestions for a topic from the intervention nurse. The meeting, which can be face-to-face or over the telephone according to the parents’ preference, is structured around the Representational Approach, that is, it assesses the representations, explores the gaps, errors, and confusions in those representations, introduces new information, sums up the new information, and sets goals. In parallel, parents receive standard care according to local procedures.

The intervention starts two months after the child has an established diagnosis. This point in time was chosen because previous research has shown that both parents and HCPs report that the most intense information provided at diagnosis has usually ceased being given by this time [4, 6, 30]. The meetings take place at approximately 8, 11, 14, and 22 weeks after the child’s diagnosis.

### Outcomes and measurements

The primary outcome for this study is illness-related parental stress as measured by the PIP [31]. Further, secondary outcomes measured are post-traumatic stress symptoms, anxiety, depression, satisfaction with information, expected and received knowledge, experiences of health care staff, and the number of health care contacts. Background demographic data is also being collected.

The PIP was originally developed in a paediatric oncology setting, but it has been used widely in different paediatric populations. It consists of 42 items that measure both the frequency and difficulty of the following four domains of stress: communication, emotional functioning, medical care, and role functioning. Each item is answered twice on a 5-point Likert-type scale, once fore frequency and once for difficulty. The range for the sum score is 42–210 points, where higher scores indicate higher frequency/difficulty [31]. The PIP has sound psychometric properties and is available in Swedish.

The *Impact of Event Scale-Revised* (IES-R) is used to measure post-traumatic stress symptoms [32]. The dimensions of intrusion, avoidance, and hyperarousal are measured on a total of 22 items with a 5-point Likert-type scale. The sum score ranges from 0 to 88 points, and higher values indicate more stress symptoms. A Swedish translation is available, and the instrument has been used in paediatric oncology previously.

*Anxiety* and *depression* are measured with two visual-digital scales. VDS-Anxiety has been used previously in this population, and it correlates with other instruments such as Spielberg’s State-trait-anxiety inventory. Parent are asked to assess if they have experienced anxiety during the last week on a 7-point Likert-type scale ranging from never to always. VDS-Depression is the equivalent measure for depression [33].

Parental *satisfaction with information* is also measured by visual digital scales. The questions are, for example, “How satisfied are you with the information you have about your child’s illness?” and “How satisfied are you with the information you get from the information sessions?”.

*Expected knowledge and received knowledge* are measured with two instruments, Knowledge Expectations of Significant Others and Received Knowledge of Significant Others [34]. Both instruments measure knowledge in 40 areas. Swedish translations are available, and the instruments have been used in several patient education studies.

*Experiences with your health care provider* are measured on a 15-item instrument developed from Swanson’s theory of caring. This instrument measures aspects of the meeting with the intervention nurse using words such as “comforting”, “informative”, “listening”, and “respectful”. The instrument has previously been translated into Swedish, and psychometric testing of the instrument is in progress.

We also ask the parents for the number of *contacts with the health care* system and what questions were asked by the parents during these contacts. *Summaries of the intervention meetings* are written by the intervention nurses after each meeting. These include the topic that was discussed, the duration of the meeting, what components of the representational approach were used, technical problems, and so on.

Parents also report *background demographic data* such as age, occupation, position in the family, and previous experiences of cancer illness. For the ill child, data about age, sex, and diagnosis are collected.

### Data collection

Data for the instruments are collected using the open-source web survey application LimeSurvey version 2.05. Invitations and reminders are sent out via e-mail and mobile text messages, and the questionnaires can be answered on a computer, tablet, or smart phone by following a hyperlink in the text message or e-mail. Paper questionnaires are provided for participants preferring that.

### Process evaluation

Contemporaneously with the evaluation of the effect of the intervention, we perform a process evaluation. This aims at understand how and why the intervention does or does not work and to describe experiences of parents as well as the intervention nurses [35]. In this part, we will examine how the intervention is performed by the nurses and how well they adhere to the intervention manual via self-reporting and the audio recordings of interview sessions. Approximately one third of the parents participating in the intervention arm are followed more closely during the intervention through recurrent qualitative interviews about their experience of participating. All intervention nurses will participate in focus group interviews. Each intervention meeting is also documented by the intervention nurses, including reflections on the intervention process.

### Data analysis

Quantitative data will be analysed using the SPSS statistical software package. Continuous variables will be reported as the arithmetic mean ± standard deviation, and categorical variables will be reported as the frequency and percentage. Differences between the trial arms will be evaluated using Student’s *t*-test for the outcome variables at the available time points. We will also perform regression analyses using data from the process evaluation, including intervention fidelity and other contextual factors. By using multivariate techniques, we will adjust for any differences found in the baseline characteristics of the participants. When appropriate, Bonferroni adjustments will be made on the overall significance levels. For all of these analyses, effect sizes will be calculated. All analyses will employ the intention to treat principle, and two-tailed *p*-values ≤ .05 will be considered as statistically significant [36].

Qualitative data, such as individual and focus groups interviews and recorded intervention meetings, will be analysed using qualitative content analysis [37]. This method focuses on similarities and differences in data, which is useful for finding possible variances in intervention performance that might explain differences in outcomes.

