### Hypothesis and aims

The aim of this paper is to describe the design of a multi-centre randomized controlled trial that longitudinally evaluates an intervention with person-centred information for parents of children with cancer.

The hypothesis of the study described here is that an intervention with person-centred information emanating from the parents’ own information needs and their current knowledge is associated with reduced illness-related parenting stress, reduced post-traumatic symptoms, reduced depression, reduced anxiety, increased received knowledge, higher satisfaction with information, and reduced number of health care contacts among the participating parents compared to a control group that receives standard care.

A secondary aim of the study described in this paper is to explore the parents’ and intervention nurses’ experiences of participating in the intervention and to describe the contextual factors that influence the intervention’s effect.

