## Methods/Design

### Design

The study is a multi-centre randomized controlled trial with two parallel arms and a 1:1 allocation ratio. One arm receives the intervention plus standard care, and the other arm only receives standard care according to local routines at each ward. In parallel to the intervention, a process evaluation is performed to describe experiences and contextual factors of importance, such as intervention dose and fidelity to the protocol.

Both quantitative data (questionnaires – either online or on paper according to the parent’s preference) and qualitative data (interviews, reflective notes, and audio recordings of the intervention meetings) are currently being collected and analysed. The questionnaires are sent out at baseline (T0), once during the intervention (T1), and at two weeks (T2), two months (T3), six months (T4), and one year (T5) after the intervention. A schedule of the intervention is provided in Table 1.

**Table 1 Tab1:** Weekly schedule of the trial

WEEK	0	4	6	7	8	11	14	20	22	24	30	46	74
Enrolment													
Diagnosis	X												
Eligibility screening		X											
Informed consent		X											
Allocation				X									
Assessments													
Baseline			T0										
Follow-up measurements								T1		T2	T3	T4	T5
Qualitative interviews^a^							Q1			Q2			
Recording of intervention meetings^a^					X	X	X		X				
Intervention													
Intervention meetings					X	X	X		X				

^a^With a subset of participants

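### The arms are compared only by a separate t-test at each time point, so no stated analysis gives an interval for how the arm difference changes or pools the repeated measures

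*Protocol article*

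**What the plan says.** Under Hypothesis and aims, the protocol article describes a trial that "longitudinally evaluates an intervention with person-centred information for parents of children with cancer". Under Design, a baseline questionnaire (T0) is followed by one while the intervention is under way (T1), one a fortnight after it (T2), and others at "two months (T3), six months (T4), and one year (T5) after the intervention". Each parent therefore has a baseline and five follow-up measurements.

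Under Data analysis, the arms are compared by Student's t-test "for the outcome variables at the available time points". Four further sentences bear on this:

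- Regression is tied to the process evaluation: "We will also perform regression analyses using data from the process evaluation, including intervention fidelity and other contextual factors".
- Adjustment is tied to baseline imbalance: "By using multivariate techniques, we will adjust for any differences found in the baseline characteristics of the participants".
- Multiplicity is left conditional: "When appropriate, Bonferroni adjustments will be made on the overall significance levels".
- Effect sizes are promised: "For all of these analyses, effect sizes will be calculated".

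None of these mentions time, a repeated-measures model or an arm-by-time term.

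**The concern.** The same parents are followed to one year, yet the stated tests treat each time point as a separate cross-sectional comparison. Two things are lost.

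First, the change in the arm difference, for example from T2 to T5, is never estimated with an interval. If the results are read through the .05 threshold, a significant T2 beside a non-significant T5 may be taken as fading, and the reverse as a late effect. A difference in significance is not evidence of a difference in effect.

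Second, five correlated measurements on one parent carry more information about a sustained effect than any one of them. Separate tests do not use it.

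Naming a primary time point, controlling multiplicity or completing the data would leave both gaps open.

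**Working it through.** **Inputs from the article (Sample size; Design; Data analysis).** d = .5, equal to 13 PIP points, so the implied SD is 13/.5 = 26. Two-sided alpha .05, power .8, 130 parents needed, 30% loss, 180 recruited, 1:1 allocation.

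**Assumptions, not in the article.** Within-parent correlation ρ = .5 to .8, equal between all pairs of time points; equal variances; a constant effect of d = .5 at T2 to T5; independent parents.

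**The plan's own figure.** The noncentral-t formula for one two-sample comparison gives 63.8, so 64 per arm and 128 in total, in line with the stated 130. The trial is thus sized for a single t-test. With 30% loss, 180 × .7 = 126 parents remain, or 63 per arm, and one t-test then has power .795.

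**How often T2 and T5 disagree under a constant effect.** From 20,000 simulated trials per correlation, 63 per arm:

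| ρ | T2 and T5 disagree in significance |
|---|---|
| .5 | .233 |
| .6 | .202 |
| .7 | .178 |
| .8 | .144 |

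With equal numbers at each time the direction splits about evenly, so false fading occurs in roughly 12% (.233/2) to 7% (.144/2) of trials. If numbers instead fall from 85 per arm at T1 to 63 at T5 (an assumed pattern), false fading is 13% to 14% and false late emergence 3% to 7%.

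A Bonferroni level of .05/5 = .01 worsens the disagreement. With 65 per arm, power per test falls from .81 to .59. T2/T5 disagreement at ρ = .5 rises from .104 + .116 = .220 to .166 + .162 = .328, and at ρ = .8 from .077 + .072 = .149 to .100 + .102 = .202.

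**What a joint analysis would give, 63 per arm.** In SD units, the standard error of one arm difference is √(2/63) = .178.

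*Average of T2 to T5:* SE = .178 × √((1 + 3ρ)/4).
- ρ = .5: SE = .141; power = Φ(.5/.141 − 1.96) ≈ .94.
- ρ = .8: SE = .164; power = Φ(.5/.164 − 1.96) ≈ .86 (simulation .853).

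*Change, T5 minus T2:* SE = .178 × √(2(1 − ρ)).
- ρ = .5: SE = .178; 95% CI half-width = 1.96 × .178 × 26 ≈ 9.1 PIP points.
- ρ = .8: SE = .113; half-width = 1.96 × .113 × 26 ≈ 5.7 PIP points.

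Power of the change contrast:

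| True change | ρ = .5 | ρ = .8 |
|---|---|---|
| None (false-positive rate) | about .05 | about .05 |
| Complete loss of the .5 effect (simulated) | .79 | .99 |
| Loss of half (.5 to .25): Φ(.25/SE − 1.96) | .29 | .60 |

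The contrast is informative about complete loss of the effect and weak for partial loss.

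**The case against.** The case on the other side is substantial.

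- **The hypothesis names no trajectory.** It states lower stress and better secondary outcomes than control. A t-test at T5 does test whether the arms differ at one year. This stands: the tests are valid for that question.
- **Effect sizes are promised.** Their difference between time points is a point estimate of change, so significance patterns would not be the only evidence. This stands; only an interval for the change is absent.
- **A longitudinal model could sit in an analysis plan that is not shown.** It could. But the article does not merely leave the arm comparison open. It names a method, and that method does not link the time points.
- **Precision.** With complete data, a model saturated in arm and time returns the same difference at each time point as the t-tests, before any baseline term is added. This stands: the gain calculated above comes from averaging over time points, which is a different quantity.
- **Model structure.** Parents of one child are randomized to the same arm (Participants), so a model without a family term would treat co-parents as independent. This stands and is built into the fix.

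A reader might infer that a constant effect will often appear to fade or emerge late, and cite the 42% to 27% of simulated trials with any mixed pattern across T2 to T5. The documents do not support that reading. The count includes patterns such as a miss at T3 alone, which is neither fading nor late emergence, and nothing in the article says that persistence will be inferred from p-values. The T2/T5 figures are the relevant ones.

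**Conclusion.** The point holds as a worthwhile improvement to a stated method, not as an error that invalidates the planned tests. A trial described as longitudinal has no stated analysis that puts an interval on the change in the arm difference or combines the follow-up measurements.

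With 63 parents per arm and a constant d = .5, the cost is a T2/T5 disagreement in about 23% to 14% of trials, about half of it false fading, and power of about .80 for one test where the T2 to T5 average would have about .94 to .85. These figures rest on an assumed within-parent correlation of .5 to .8 and ignore family clustering.

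One might also infer that the T5-minus-T2 change could settle persistence by itself. It cannot: zero change also fits no effect at either time, so the T5 difference is needed beside it.

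**What to change.** In Data analysis, replace the row of t-tests for PIP, and for each repeatedly measured scale, with one linear mixed model over T1 to T5. Include arm, time, arm-by-time and the baseline value, with random effects or an equivalent covariance structure for parent and for child or family. From it, report:

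1. the arm difference with 95% CI at each time point;
2. the average T2 to T5 difference, as a supporting estimate;
3. the T5-minus-T2 change in the arm difference, with 95% CI.

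State that a lasting benefit will be judged from the T5 difference together with that change, not by comparing p-values across time points. State also that the change contrast has limited power for partial fading (about .29 to .60 for loss of half the effect, on the assumptions above).

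The cost is analysis wording only: the data and SPSS are already planned, and the article describes recruitment as ongoing, so the change can still be prespecified. The downside is a slightly more complex model and results table.

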### Participants

We are currently recruiting participants from two paediatric oncology tertiary care centres in Sweden. These centres cooperate with local hospitals where some of the treatment and supportive care is given; however, diagnoses and major treatments are performed at the centres. Inclusion criteria are being a parent of a child that a) is diagnosed with a first-time occurrence of a malignancy that is curatively treated and b) was diagnosed within the past two months. Furthermore, parents must be able to speak, read, and write Swedish well enough to participate without an interpreter.

All parents, including any stepparents, are being invited to participate, and interventions and measurements are being performed individually. Eligible parents are approached by a recruitment nurse at each site. After receiving information about the study, informed consent is obtained from parents willing to participate and the baseline questionnaire is distributed.

When the baseline questionnaire has been filled in, parents are randomized to one of the two study arms. Parents of the same child are randomized to the same arm to avoid contamination within couples. The allocation sequences were generated using the online service www.randomization.com. The allocation is performed by an independent person using opaque, pre-numbered envelopes. For each site, two strata are used: i) one participating parent per family and ii) two or more participating parents per family. This strategy will balance the number of parents equally between sites and arms. Both strata are blocked with randomized, varying block sizes (2, 4, or 6 units) that are blinded to the researchers and the person performing the allocation.

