### Sample size

According to a power calculation, 130 parents in total will be needed if we expect a moderate effect size (Cohen’s *d* = .5, which corresponds to 13 points of the total score of the primary outcome measure, the Pediatric Inventory for Parents (PIP)), α = .05, and statistical power = .8. We expect that 30 % of parents will not finish the study, meaning that 180 parents in total need to be recruited.

For the qualitative interviews, we plan to interview one third of the parents (*n* = 20) allocated to the intervention arm.

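### Covariates chosen from observed baseline imbalance, with no fixed adjustment for baseline PIP or the randomisation strata, give up available precision and leave room for post-hoc choice

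*Protocol article*

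**What the plan says.** The Data analysis section evaluates differences between arms with Student's t-test on the outcome variables at the available time points. It then says that multivariate techniques will be used, by which "we will adjust for any differences found in the baseline characteristics of the participants". It names no covariate, no criterion for what counts as a difference, and no rule for which result decides the trial.

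Two kinds of baseline information are available without further work:

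- **Baseline outcome.** "The primary outcome for this study is illness-related parental stress as measured by the PIP" (Outcomes and measurements), and the order of events is that "When the baseline questionnaire has been filled in, parents are randomized to one of the two study arms" (Participants). I read the T0 questionnaire as including the PIP, since the Design section sends the questionnaires out at T0 and at every later time point.
- **Stratification factors.** "For each site, two strata are used: i) one participating parent per family and ii) two or more participating parents per family" (Participants).

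Neither is named in the stated comparison. The sample size rests on d = .5, "which corresponds to 13 points of the total score of the primary outcome measure", with "α = .05, and statistical power = .8", and makes no allowance for covariate adjustment.

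**The concern.** Under randomisation, baseline differences between the arms arise by chance. A covariate is worth including when it predicts the outcome, whether or not it happens to be unbalanced. The stated rule works the other way round: the baseline value of the primary outcome, likely the strongest predictor to hand, enters only if the arms happen to differ on it.

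Three things are at stake. First, precision that the trial has already paid for is not used. Second, because the text gives no threshold and no decisive analysis, the choice between adjusted and unadjusted results can be made after seeing both. Third, stratified randomisation balances site and family type across the arms. An analysis that ignores them does not credit that balance if they are prognostic.

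**Working it through.** **Inputs.** From Sample size: a 13-point difference at d = .5, so SD = 13/.5 = 26; α = .05; power .80; 130 evaluable and 180 recruited with 30% loss. From Data analysis: two-sided testing, where "values ≤ .05 will be considered as statistically significant". From Design: 1:1 allocation. The correlation r between T0 and follow-up PIP is not in the document, so I assume .3 to .7. All figures treat parents as independent.

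**The plan's own figure.** A two-sample t-test at d = .5, two-sided .05, power .80 needs 63.8, so 64 per arm or 128 in total, close to the stated 130. Power at 65 per arm is .808. With 30% loss, 180 × .70 = 126 completers, or 63 per arm, and power is .795.

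**Prespecified ANCOVA on T0 PIP.** Residual SD = 26 × √(1 − r²), so the effective d = .5/√(1 − r²). With 63 per arm:

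| r | Residual variance (1 − r²) | Effective d | Power |
|---|---|---|---|
| t-test, no adjustment | 1.00 | .500 | .795 |
| .3 | .91 | .524 | .831 |
| .4 | .84 | .546 | .860 |
| .5 | .75 | .577 | .895 |
| .6 | .64 | .625 | .936 |
| .7 | .51 | .700 | .974 |

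**What the stated rule delivers.** The text gives no criterion, so one concrete version was simulated: adjust for T0 PIP only if its baseline difference has p ≤ .05, and otherwise use the t-test. There were 20,000 trials per scenario with 65 per arm.

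| r | Power: t-test | Power: adjust if p ≤ .05 | Power: prespecified ANCOVA | Type I error: adjust if p ≤ .05 | Type I error: better of t-test and ANCOVA |
|---|---|---|---|---|---|
| .3 | .810 | .813 | .842 | .048 | .063 |
| .5 | .804 | .813 | .902 | .045 | .075 |
| .7 | .804 | .825 | .975 | .035 | .083 |

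The mechanical rule stays close to the t-test in power and does not exceed 5% type I error. The last column applies only if the adjusted result can be reported whatever the observed imbalance. If the choice is limited to the t-test or the p ≤ .05 rule, type I error is only .051 to .054.

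**Strata.** If site or family type predicts PIP, the t-test keeps between-stratum variation in its error term although the design has balanced it, so the standard error is too large. The document gives no site or family-type effect, so the size cannot be computed.

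**The case against.** The best defence is that an unadjusted t-test is valid in a randomised trial and that the sample size was set for exactly that test. This stands: 130 evaluable parents give about .81 power, and nothing here shows a shortfall against the stated power.

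A reader might infer more than the documents support:

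- **That the rule invalidates the p-value.** It does not when applied mechanically; type I error was .035 to .048. Inflation needs a free choice between results. The text does not announce such a choice, but it does not exclude one either.
- **That ignoring the strata gives false positives.** The usual direction is the opposite: too large a standard error and some lost precision.
- **That chance imbalance in T0 PIP is an added error.** Its standard error is 26 × √(2/n), or 3.9 points at 90 per arm and 4.6 at 65. Setting that against the 13-point target double-counts, because the t-test's standard error already contains this variation.
- **That adjustment would pay for clustering by family.** With an assumed design effect of 1.3, ANCOVA power at 63 per arm is .803 at r = .5 but .757 at r = .4. Clustering is a separate matter.

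It is also fair to say that r is assumed. T0 is at week 6 and T2 to T5 run from week 24 to week 74, so the upper end of the range has no support in the document, and at r = .3 the gain is small.

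Finally, an article may leave its covariate list to a fuller plan. That covers the absence of a list. It does not cover the rule that is stated, which ties adjustment to what the data show.

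**Conclusion.** The point holds as a free improvement. The stated rule selects covariates on the wrong criterion, recovers almost none of the precision in T0 PIP, and leaves open which result decides. With 63 completers per arm and d = .5, prespecified ANCOVA would raise power from .795 to .83 at r = .3, .90 at r = .5 and .97 at r = .7. These figures depend on the assumed r and on independent parents. If the better of a t-test and a T0-adjusted result were reported, type I error would be about .063 to .083 over the same range. That describes what the wording permits, not what the plan says it will do. The benefit from including the strata is real only if they are prognostic, and it cannot be sized here. The stated power and the validity of the t-test are not in question.

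**What to change.** Make the primary analysis one prespecified ANCOVA or mixed model for PIP with arm, T0 PIP, site and one versus two-or-more participating parents, fitted whatever the observed balance, and state that this result decides. Use the same model, with its own T0 value, for each secondary outcome that has one. Delete the rule based on observed differences, or keep it only as a labelled sensitivity analysis with covariates named in advance.

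The cost is analysis wording alone. T0 scores and strata are already recorded, and no extra parents, visits or questionnaires are needed. The article describes recruitment as ongoing, so the model can be fixed before outcomes are compared between arms.

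### Separate t-tests at each time point, sized on finishers after 30% loss, do not back the intention-to-treat statement with an analysis of all randomised parents

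*Protocol article*

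**What the plan says.** The Data analysis section fixes the comparison of arms: "Differences between the trial arms will be evaluated using Student’s *t*-test for the outcome variables at the available time points". It then commits to a principle for everything that follows: "All analyses will employ the intention to treat principle". Regressions are also planned, but the baseline adjustment covers only differences that turn out to exist.

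The Sample size section states that "130 parents in total will be needed if we expect a moderate effect size", with the effect given as 0.5 SD, "which corresponds to 13 points of the total score of the primary outcome measure", and with "α = .05, and statistical power = .8". It continues: "We expect that 30 % of parents will not finish the study, meaning that 180 parents in total need to be recruited".

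Two features of the design matter here. Under Participants, allocation follows completion of the baseline questionnaire, and families are allocated as units. Under Design, there are five follow-up questionnaires after T0, the last (T5) at week 74 of the schedule in Table 1. No section of the article names imputation, a repeated-measures model or a sensitivity analysis for missing outcomes.

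**The concern.** A t-test at one time point can use only parents who have a value at that time point. With 30% expected not to finish, a large minority of randomised parents would be absent from the last comparison, and the set of parents compared may change from T1 to T5. Every randomised parent should have a T0 score, and many who leave will have follow-up scores as well, but the test at T5 uses none of these.

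The primary outcome is self-reported illness-related stress, and a parent's stress may well affect whether the questionnaire comes back. The arms also differ in contact with the study: four nurse meetings plus standard care, against standard care alone. The amount of loss, or the kind of parent lost, could therefore differ by arm. If it does, the estimated effect is biased, in a direction that depends on which arm loses the more stressed parents. Even without bias, information already collected goes unused in the later comparisons.

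**Working it through.** **Inputs from the protocol article.** Sample size section: d = 0.5, equal to 13 PIP points, so SD = 13 / 0.5 = 26; α = 0.05; power 0.80; 130 parents needed; 30% loss; 180 recruited. Data analysis section: two-sided tests. Design section: 1:1 allocation. I take all 180 recruits as randomised, 90 per arm.

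**Step 1: reproduce the plan's figures.**
- Normal approximation: n per arm = 2(1.96 + 0.84)² / 0.5², which rounds up to 63, or 126 in total.
- Exact t-test: 63.8, rounded up to 64 per arm, or 128 in total. The stated 130 is consistent with this.
- Recruitment as N / (1 − 0.30): 126 / 0.7 = 180; 128 / 0.7 = 183; 130 / 0.7 = 186. The stated 180 matches the requirement before it was rounded up to 130.

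**Step 2: whose power is it?** 180 × 0.7 = 126 finishers. Power with 126 at d = 0.5 is 0.80 (0.795 by the exact t-test). Complete data on all 180 would give 0.92. The planned 80% is thus the power of a test on finishers. Both figures treat parents as independent.

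**Step 3: parents absent from the final test.** 180 × 0.30 = 54, if not finishing means having no PIP score at T5. Losses at earlier time points may be smaller.

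**Step 4: when is the arm difference biased?** In one arm let m be the share lost, and let δ be the mean of those lost minus the mean of those observed. The full mean is (observed mean) + mδ, so the observed mean is too low by mδ. The bias in the arm difference is the gap between the two arms' values of mδ. It is zero when m and δ are the same in both arms, however large they are.

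**Step 5: size under assumed values.** The documents give neither m nor δ by arm. I assume a true effect of zero, SD 26 and δ of 0.25, 0.5 or 1.0 SD (6.5, 13 or 26 points). Type I error is for a nominal two-sided 0.05.

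| Assumed loss and selection | Bias in PIP points | Type I error |
|---|---|---|
| 30% in both arms, same δ | 0 / 0 / 0 | 0.05 |
| 25% vs 35%, same δ | 0.65 / 1.3 / 2.6 | not computed |
| 20% vs 40%, same δ | 1.3 / 2.6 / 5.2 | 0.06 / 0.09 / 0.20 |
| 30% in both arms, δ in one arm only | 1.95 / 3.9 / 7.8 | 0.07 / 0.13 / 0.39 |

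Example for the third row, middle value: 0.40 × 13 − 0.20 × 13 = 5.2 − 2.6 = 2.6 points, and 2.6 / 13 = 20% of the target effect. The groups observed are 90 × 0.8 = 72 and 90 × 0.6 = 54. If control loses more of its stressed parents, the benefit is understated; if the intervention arm does, it is overstated.

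**The case against.** The strongest reply is that the text does not say what a reader might infer from it. Three stronger readings are tempting, and the documents support none of them.

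- *The plan declares a complete-case analysis that contradicts intention to treat.* In the t-test sentence, the word available qualifies time points, not parents, and nothing rules out imputation before the test. Intention to treat in the sense of analysing parents in the arm to which they were allocated is compatible with a t-test. The article does not define the term.
- *Thirty percent loss biases the result.* Step 4 shows otherwise. Loss related to stress leaves the arm difference unbiased when its amount and its selection are the same in both arms.
- *Data from parents who leave are thrown away.* They count at every time point at which those parents responded. They only fail to inform the later tests.

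It is also fair to say that a condensed article may leave missing-data handling to a fuller document, so the absence of a named method is not by itself a fault.

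All of this stands, and it limits the point without removing it. The article does fix a between-arm method, and its recruitment target is the one that gives 80% power to a test on finishers, which favours the observed-scores reading without proving it. The planned regressions do not close the gap: adjustment depends on differences being found, and an ordinary regression at one time point also omits parents with no outcome there.

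**Conclusion.** The point holds in a limited form. Taken as written, each test uses observed scores only. About 54 of 180 randomised parents would be missing from the final comparison, and their T0 and earlier follow-up scores would not contribute to it. The intention-to-treat statement is therefore not backed by an analysis of all randomised parents.

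Bias is a risk and not a demonstrated result. It requires loss, or the relation of loss to stress, to differ between arms, and the documents give no figures on either. Over the assumed scenarios it runs from 0 to 7.8 PIP points, and from 1.3 to 5.2 points in the 20% versus 40% case. The count of 54 rests on the plan's own 30%, on all recruits being randomised and on no imputation. The change is worth making because the stated method can be replaced, at little cost, by one that uses data the trial already collects.

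**What to change.** Replace the separate t-tests, for the primary outcome, with a likelihood-based repeated-measures mixed model on the T0–T5 PIP scores. Include arm-by-time terms and a family random effect, the latter because parents of one child share an allocation. Enter T0 either as a covariate or within a constrained longitudinal outcome vector, with arm means held equal at T0. The constrained version brings in every randomised parent, since T0 precedes allocation. The covariate version brings in every parent with at least one follow-up score.

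This model uses all observed data, is valid under missing-at-random, and gains precision to the extent that T0 and earlier scores predict later ones. The documents give no such correlation, so I put no figure on the gain; it will not restore the full 0.92 power of complete data.

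The model does not remove bias from drop-out that depends on unobserved stress. Add one delta-adjusted multiple-imputation sensitivity analysis in which the shift for missing scores may differ by arm, and report numbers observed by arm at each time point.

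The cost is revised wording and a little more programming. SPSS, the software named in the plan, can fit the mixed model, and no new data are needed.
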